### Study population

2.2

Participants who meet the eligibility criteria and sign informed consent will be enrolled in the study. Inclusion criteria for enrollment are described as follows:

(1)males or females aged 16 to 65 years old;(2)agree to participate in the research and sign the informed consent form;(3)the subjects biological parents are Han;(4)diagnosed with bipolar depressive disorder according to the fourth Edition of Diagnostic and Statistical Manual of Mental Disorders diagnostic criteria;(5)score more than or equal to 17 points on the Hamilton depression scale at screening and baseline period;(6)score less than or equal to 5 points on the young mania rating scale (YMRS) at screening and baseline period;(7)no taking any drug treatment or no receiving antidepressant treatment in the last 1 month;(8)take drugs by oneself during the study period, or have a regular helper to help with the medication.

Exclusion criteria are described as follows:

(1)diagnosed with other spectrum disorders according to the fourth Edition of Diagnostic and Statistical Manual of Mental Disorders diagnostic criteria;(2)mental disorder caused by substance abuse, or serious physical diseases;(3)received antibiotics within 1 month before enrollment due to respiratory tract, urinary tract, the digestive system infection;(4)subjects with a history of attempted suicide, or currently at high suicide risk, or with suicide behavior/attempt, or scoring more than or equal to 3 points on the 10th clause of Montgomery Asberg Depression Rating Scale (MADRS);(5)unwilling to take the medicine;(6)known pregnancy, lactation, or pregnant planning;(7)the subjects with contraindications of quetiapine or have used quetiapine but have poor efficacy;(8)allergic to broccoli;(9)received electroconvulsive therapy within 1 month.

Suspension criteria are as follows:

(1)subjects with serious adverse drug reactions;(2)exchange drugs or receive other treatment due to unstable condition;(3)refuse to continue participating in the study;(4)lose track in follow-up;(5)other factors cause the interview to stop.

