### Outcomes

2.5

Primary outcome is the change in the MADRS scores at baseline compared to each treatment time point. MADRS is a clinician-administered rating scale and widely used to assess the depression severity of patient with BD. The response was defined as at least a 50% reduction when compared to baseline in the scores.

While secondary outcomes include the scores of the quick inventory of depressive symptomatology-self report, Hamilton anxiety rating scale, and YMRS scores are used to elevate the broader affective symptoms. Besides, cognitive function which tested by THINC-integrated tool, inflammatory factors (interleukin-2, interleukin-4, interleukin-6, interleukin-10, interleukin-17A, tumor necrosis factor and interferon-γ) and intestinal flora are used to investigate the underlying biological factors.

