### Safety assessment

2.6

Vital signs, body mass index, the liver and kidney function, levels of serum electrolytes, blood glucose and lipids, blood cell counts, and electrocardiograms will be conducted on all participants. At each participant's visit, AEs will be assessed. The severity of AEs were assign as mild, moderate, severe, or serious. We will record the onset date, end date, severity, the relationship with the clinical trial, the outcomes, and the measures adopted in the AEs form and provide appropriate treatment if any AEs occur during the study process. The trial will be stopped in case of treatment-related suspected unexpected serious AEs.

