### Statistical analysis

2.8

All statistical analyses will be performed using SPSS 19.0 software (IBM, Armonk, NY) in a blinded manner. Outcomes will be analyzed on the basis of intention-to-treat principle. Missing values will be handled by the practical guide described by Jakobsen et al. The comparison of primary outcomes and secondary outcomes between 2 groups will be performed by *t* test for continuous variables and *χ*^2^ test for categorical variables, or with Wilcoxon Mann–Whitney test. The paired *t* test will be used for analysis in each group. *P* < .05 will be considered significant

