## Discussion

3

As a chronic and complex mood disorder, the treatment of BD frequently required combinations of therapies. A number of pharmacotherapeutic treatments with side effects induce low adherence of patient and poor outcomes. Nutraceutical agents with higher acceptability are more and more considered to improve treatment for the symptoms of BD as adjunctive therapies.^[29]^ In the treating mental disorders, SFN has been proved have a significant improvement in mood and cognitive function by regulating peroxidation reactions.^[25,30]^ The aim of this randomized clinical trial is to investigate the effect of SFN as an adjuvant role in the treatment of bipolar depressive disorder.

In this study, besides using the MADRS, Hamilton depression scale, Hamilton anxiety rating scale, quick inventory of depressive symptomatology-self report, and YMRS scales to assess the clinical curative effect on emotional problem, THINC-integrated tool will be introduced to evaluate neurological status. In addition, we monitor inflammatory factors including serum concentration of and intestinal flora before and after treatment to explore the possible mechanism of SFN combined with quetiapine on treating bipolar depressive disorder. In summary, we expected that our findings will provide evidence for efficacy and safety of SFN as an adjuvant treatment of BD.

This study also has some limitations. First, this is an exploratory trial with evaluating the intervention by various outcomes and process measures from multiple perspectives, the results should be cautiously interpreted. Besides, as a nutritional supplement, the dose of SFN in the preliminary study is conventional, but perhaps that's not necessarily a most effective dose. Thus, further study is required to explore an optimal dose plan for SFN as an adjuvant in the treatment of bipolar depressive disorder.

In summary, this trial is expected to provide initial findings on the synergistic effect of SFN in the treatment of BD. If, as expected, combination of quetiapine and SFN therapy could have more positive effects, it will provide an opportunity to increase the availability of evidence treatment for patients with BD.

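### YMRS is capped at 5 on entry, yet it is listed among curative outcomes and compared as a score; it serves better as a safety measure of mood switch, reported as patients per arm

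*Protocol article*

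**What the plan says.** Inclusion criterion 6 (protocol article, section 2.2) requires patients to "score less than or equal to 5 points on the young mania rating scale (YMRS) at screening and baseline period".

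Section 2.5 places YMRS among the secondary outcomes: "Hamilton anxiety rating scale, and YMRS scores are used to elevate the broader affective symptoms" (the verb is evidently a slip for evaluate). The Discussion groups it with four other scales and describes the use of "YMRS scales to assess the clinical curative effect on emotional problem".

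Section 2.8 sets the analysis: "The comparison of primary outcomes and secondary outcomes between 2 groups will be performed by" t test for continuous variables and chi-square test for categorical ones, "or with Wilcoxon Mann–Whitney test". A paired t "test will be used for analysis in each group".

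Section 2.6 lists vital signs, laboratory tests, electrocardiograms and adverse events. It says "At each participant's visit, AEs will be assessed", but names neither YMRS nor a switch into mania or hypomania. One suspension criterion in section 2.2 reads "exchange drugs or receive other treatment due to unstable condition".

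**The concern.** The entry rule and the outcome's stated role pull in opposite directions. Patients are selected, at both screening and baseline, to have essentially no manic symptoms, so there is no mania to cure. In a bipolar depression trial the informative change in YMRS is a large rise in a few patients, which is a harm.

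A comparison of means averages those few rises with many small movements near zero. A rank test largely ignores how big the rises are. The article promises evidence on both efficacy and safety. A flat YMRS comparison could be taken as absence of mood destabilisation, and small shifts at the floor could be taken as benefit, while more patients on sulforaphane had switched.

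**Working it through.** The documents give no YMRS distribution, switch rate or YMRS result, so there is no stated figure to reproduce. From the documents come the entry ceiling of 5, 50 patients per arm and 10% dropout, hence 50 × 0.9 = 45 evaluable per arm. All other inputs are assumptions.

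**1. Room to improve.** The largest fall for any patient is 5 − 0 = 5 points. If baseline is uniform on 0 to 5, the largest possible mean fall is the baseline mean, 2.5.

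**2. Cancellation in the mean.** Suppose switchers rise by 20 points, with 45 per arm.
- Two switchers: 2 × 20 / 43 = 0.93. A fall of 0.93 points in each of the other 43 brings the mean change to zero.
- Three switchers: 3 × 20 / 42 = 1.43 points in each of the other 42.

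**3. Expected mean change.** Assume baseline uniform on 0–5 (mean 2.5), non-switchers uniform on 0–4 at follow-up (mean 2.0, change −0.5), and switchers at 16–26 (mean 21, change +18.5). Where a floor-level fall on sulforaphane is added, each non-switcher loses 1 point but not below 0. The values 0, 1, 2, 3, 4 become 0, 0, 1, 2, 3 (mean 1.2, change −1.3).
- Placebo, 2% switching: 0.98 × (−0.5) + 0.02 × 18.5 = −0.12
- Sulforaphane, 6% switching with the fall: 0.94 × (−1.3) + 0.06 × 18.5 = −0.11

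Three times as many patients switch, and the means are practically equal.

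**4. Simulated tests on change, same model, 45 per arm, two-sided 5%.**

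| Switching, sulforaphane vs placebo | Floor-level fall on sulforaphane | t test significant | Mann–Whitney favours sulforaphane | Mann–Whitney goes against it |
|---|---|---|---|---|
| 10% vs 2% | none | 27.4% | – | – |
| 10% vs 2% | up to 1 point | 8.6% | about 13% | 0.3% |
| 6% vs 2% | up to 1 point | 6.0% | about 22% | 0.1% |

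The reversal in the rank test depends on the floor-level fall. A second model without it (baseline and non-switchers uniform on 0–5, switchers at 15–25) shows only insensitivity. At 14% vs 4% switching, power is 31% for the t test and 13% for Mann–Whitney.

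**5. Can YMRS favour sulforaphane?** Yes. In the model of step 3, 2% switching on sulforaphane vs 20% on placebo gives 77% t-test power. With equal 2% switching and only the floor-level fall, power is 24% (t test) and 35% (Mann–Whitney).

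**6. Would a test on switch counts be more powerful?** Not in general. In the second model, Fisher's exact test has 23% power and an uncorrected chi-square test 43% at 14% vs 4%, against 31% for the t test. At 10% vs 2% without the fall, Fisher has about 15% and the t test about 26%. In the step 3 model, at 6% vs 2% with the fall, Fisher rejects in about 2% of trials and the t test in 6%. Fisher overtakes the t test at 10% vs 2% with the fall (about 16% against 9%).

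**7. Width of the interval.** With 5 of 50 against 1 of 50, the risk difference is 0.10 − 0.02 = 0.08. Its approximate standard error is √(0.10 × 0.90/50 + 0.02 × 0.98/50) = 0.047, so the 95% interval is roughly 0.08 ± 0.09, about −1% to 17%. An exact interval would differ somewhat but would also be wide.

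**The case against.** Four objections carry weight.

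- **A reader might infer that YMRS cannot show a benefit at all.** The documents do not support that. Fewer switches on sulforaphane, or small falls within 0 to 5, could each produce a difference (step 5). What holds is that there is almost no room for a clinically meaningful fall.
- **A reader might infer that switches would go unrecorded.** Adverse events are assessed at each visit, so a switch can be captured there, and suspension for an unstable condition may record others. What remains is that the safety section does not assign YMRS to that purpose. The suspension rule could also remove switchers from later score comparisons.
- **The masking figures use chosen inputs.** Near-equal means need a floor-level effect of about the right size. The illustration shows that masking and a misleading direction are possible, not that they are likely.
- **The curative label comes from one loosely worded Discussion sentence, and a switch definition may sit in a full protocol or SAP that is not shown.** Its absence from a condensed article is no finding. But section 2.5 itself gives YMRS scores an outcome role, and section 2.8 itself applies score tests to such outcomes. A definition elsewhere would not change that.

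**Conclusion.** The point holds as a mismatch between the entry criterion and the role and analysis that the article gives to YMRS. Improvement is limited to 5 points per patient by design. Two or three large rises among 45 patients can be offset by average falls of about 0.9 to 1.4 points in the rest. Under the assumed floor-level fall, the rank test can favour the arm with more switches. The 5-point limit follows from the document; the remaining figures depend on assumed distributions and switch rates.

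It would go too far to call the YMRS analysis incapable of a favourable result, or to claim that counting switches gives a stronger test. The case for change is that a count of switches answers the relevant question in a readable form. This concerns one secondary outcome in a trial that calls itself exploratory. The primary outcome and data collection are unaffected, so it is an inexpensive improvement and not a fatal flaw.

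**What to change.** - In section 2.5, take YMRS out of the outcomes read as efficacy. In section 2.6, name it as a safety measure.
- In section 2.8, report by arm the number of randomised patients with treatment-emergent mania or hypomania at any visit, under a definition fixed before unblinding, with the risk difference and an exact 95% CI. State how patients suspended for an unstable condition enter that count.
- Keep the comparison of YMRS scores as description only.
- Remove YMRS from the list of curative measures in the Discussion.

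The cost is wording: YMRS is already collected, and treatment, visits and sample size do not change. The trial gives up one outcome presented as efficacy. With 45 to 50 patients per arm and a rare event the interval will be wide, and no gain in power should be promised.

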### Sample size

2.7

It was absent of direct evidences to support t our hypothesis, consequently, estimating the sample size is difficult. At an 8-week study, the response rate of quetiapine in BD patients was 58.9%, and the remission rate was 42.1%.^[28]^ Combination therapy has been shown to be more effective. We estimated the effective rate of SFN combined with quetiapine in the treatment of bipolar depressive disorder to be about 70%. The sample size with 80% power at a significance level of 0.05 was calculated in this study. Anticipating a 10% dropout rate, a total of 100 patients, with 50 patients in each group, will be needed.

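### The stated comparison of the seven cytokines names neither a log scale nor the baseline value, and would lose power if the concentrations are right-skewed (minor)

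*Protocol article*

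**What the plan says.** Section 2.5 (Outcomes) places the "inflammatory factors (interleukin-2, interleukin-4, interleukin-6, interleukin-10, interleukin-17A, tumor necrosis factor and interferon-γ") among the secondary outcomes. Together with cognition and intestinal flora they "are used to investigate the underlying biological factors".

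Section 2.8 (Statistical analysis) gives one rule for all outcomes. "The comparison of primary outcomes and secondary outcomes between 2 groups will be performed by" a t "test for continuous variables and" a chi-squared test for categorical ones, "or with Wilcoxon Mann–Whitney test". A P value "< .05 will be considered significant". A paired t test is added within each arm; it uses the baseline value but does not compare the arms.

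The Introduction and the Discussion both say that inflammatory factors are measured before and after treatment, so a baseline value exists for each cytokine. Section 2.8 mentions no transformation and no baseline-adjusted model, and does not say when Mann–Whitney replaces the t test. The article gives no SD, distribution, assay or expected effect for any cytokine.

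**The concern.** Concentrations cannot be negative and may have a long right tail, and a treatment may change them by a proportion rather than by a fixed amount. If so, a few high values dominate an arithmetic mean difference and its standard error, and a t test on measured concentrations or on their raw change is inefficient. Separately, a two-sample test on follow-up values ignores the variation that the patient's own baseline explains.

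What is at stake is sensitivity. The cytokines carry the mechanistic aim: the Introduction proposes that sulforaphane acts by inhibiting inflammatory cytokine production. A real fall could be missed with samples in which a better-matched analysis would have shown it.

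**Working it through.** **The plan's own figure.** There is none for the cytokines. The sample size in section 2.7 rests on response rates and does not bear on this point.

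**Inputs from the article.** 50 patients per arm and 10% dropout (section 2.7), so 50 × 0.9 = 45 per arm. Significance level 0.05 (section 2.8); two-sided is assumed, as the article does not say.

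**Assumed inputs.** Log-normal concentrations; a true 35% fall, which is ln(0.65) = −0.431 on the log scale; correlation 0.6 between log baseline and log week-12 values; log-scale SD of 0.6, 0.8, 1.0 or 1.3.

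**Check by formula at log-SD 1.0.** For a log-scale analysis, power ≈ Φ(|ln 0.65| / SE − 1.96), with SE = σ√(2/45) = 0.2108σ.

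- Log t test on week-12 values, σ = 1.0: 0.431/0.2108 = 2.04; Φ(0.08) = 53%.
- Log t test on change, σ = √(2(1 − 0.6)) = 0.894: 2.04/0.894 = 2.28; Φ(0.32) = 63% (simulated 62%).
- Log model with log baseline, σ = √(1 − 0.6²) = 0.8: 2.04/0.8 = 2.55; Φ(0.59) = 72%.

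**Simulated power across the assumed skew.** Simulation error is about 1 point (standard error √(0.5 × 0.5/4000) = 0.8 points for 4,000 trials), and repeat runs agree to within about 2 points.

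| Log-SD | t test, raw change | Mann–Whitney, week-12 values | Log model with log baseline | Shortfall (points) |
|---|---|---|---|---|
| 0.6 | 83% | 91% | 99% | 8–16 |
| 0.8 | 50% | 68% | 86% | 18–36 |
| 1.0 | 30% | 51% | 72% | 21–42 |
| 1.3 | 15% | 32% | 47% | 15–32 |

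**Where the shortfall comes from, at log-SD 1.0.**

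| Analysis | Power |
|---|---|
| t test, raw change | 30% |
| t test, raw week-12 values | 38% |
| Raw week-12 values with raw baseline as covariate | 47% |
| Mann–Whitney, raw change | 46% |
| Mann–Whitney, week-12 values | 51% |
| Log t test, week-12 values | 53% |
| Log t test, change | 62% |
| Log model with log baseline | 72% |

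For the t test on raw week-12 values, the log scale alone raises power from 38% to 53%, baseline adjustment alone to 47%, and both together to 72%. For Mann–Whitney on week-12 values, scale accounts for 53 − 51 = 2 points and baseline adjustment for 72 − 53 = 19.

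**Type I error.** With no true effect (log-SD 1.0), every method rejected in 4–6% of trials.

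**The case against.** The strongest reply is that section 2.8 names tests and not a scale. A t test on log values fits its wording, the choice of transformation per biomarker is often left to the analysis plan, and that plan is not shown. This stands against any claim that the article commits to raw concentrations. It does not dispose of the point: the article does fix the form of the comparison, an unadjusted two-sample test, for outcomes whose baseline it collects.

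The second reply is that Mann–Whitney already deals with skew. On week-12 values this is right. Ranks do not change under a log transformation, and the test is within 1 to 3 points of a log t test. It does not carry over to change from baseline, because ranks of raw differences do change. At log-SD 1.5 with a shift of 0.6 SD, Mann–Whitney on raw change holds up against a log t test on change when concentrations rise (77% against 81% at correlation 0.5; 92% against 95% at 0.7). When they fall, the direction the Introduction expects for inflammatory cytokines, it does not (55% against 80%; 75% against 96%). However, section 2.5 defines change from baseline only for the MADRS, so raw change is a possible reading for the cytokines and not a stated one.

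Third, the SDs, effect and correlation are assumed. That stands, and at log-SD 0.6 the loss is modest.

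A reader might also fault the article for giving no rule on values below the detection limit. That is commonly left to the analysis plan or laboratory manual and is no finding here.

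**Conclusion.** The point holds as a minor one. As written, section 2.8 compares the cytokines without a log scale or the baseline value. If they are right-skewed, power is lower than it need be: by 8 to 16 points at log-SD 0.6 and by 21 to 42 points at 1.0, depending on which permitted test is used and on what quantity. These sizes rest on log-normal data, a 35% fall, correlation 0.6 and 45 patients per arm.

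A reader might infer that the plan loses up to half its power. The figures do not support that as a limit: at log-SD 1.3 the t test on raw change has 15% against 47%, a loss of more than half, while at 0.6 it has 83% against 99%. Nor is the whole gap one of scale, since for Mann–Whitney on week-12 values nearly all of it is missing baseline adjustment. No excess of false positives follows.

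The severity is minor and the change optional, because the cytokines are secondary, the sample size does not rest on them, and the Discussion calls the trial exploratory and asks for cautious interpretation. At log-SD 1.3 even the better model reaches only 47%, so it does not make the cytokine comparison well powered in every case.

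**What to change.** In section 2.8, state that each cytokine is compared between arms by a linear model on log concentration with log baseline concentration as covariate, and reported as a geometric mean ratio with 95% confidence interval. Keep the Mann–Whitney test as a sensitivity analysis.

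The cost is a sentence or two, settled before unblinding. No further samples or patients are needed, and the model runs in the SPSS software already named. The small downside is that results are ratios between arms rather than differences in concentration. If the unseen analysis plan already specifies such a model, a cross-reference in 2.8 is enough.

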### Safety assessment

2.6

Vital signs, body mass index, the liver and kidney function, levels of serum electrolytes, blood glucose and lipids, blood cell counts, and electrocardiograms will be conducted on all participants. At each participant's visit, AEs will be assessed. The severity of AEs were assign as mild, moderate, severe, or serious. We will record the onset date, end date, severity, the relationship with the clinical trial, the outcomes, and the measures adopted in the AEs form and provide appropriate treatment if any AEs occur during the study process. The trial will be stopped in case of treatment-related suspected unexpected serious AEs.

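### Section 2.6 places seriousness on the adverse event severity scale, so a serious event either loses its intensity grade or is not flagged as serious

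*Protocol article*

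**What the plan says.** Section 2.6 (Safety assessment) of the protocol article sets the grading in one sentence: "The severity of AEs were assign as mild, moderate, severe, or serious". It then describes what is captured for each event: "We will record the onset date, end date, severity, the relationship with the clinical trial, the outcomes, and the measures adopted in the AEs form".

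Two rules use the word *serious*. The first suspension criterion in section 2.2 (Study population) reads "subjects with serious adverse drug reactions". The closing sentence of section 2.6 reads "The trial will be stopped in case of treatment-related suspected unexpected serious AEs". Neither rule refers to the grading list, and the article does not say what makes an event serious.

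**The concern.** Intensity and seriousness answer different questions. Intensity is how strong the event was. Seriousness is whether it met an outcome criterion, for example death, a threat to life or admission to hospital. An event of moderate intensity can lead to admission and so be serious. An event can also be severe without being serious.

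Section 2.6 treats the two as steps of one scale, with *serious* as the last level of an item labelled severity. If each event receives one value from that list, an event that is serious by outcome cannot be described fully. Two things are at stake. One is the safety record: safety is a stated aim of the trial (Introduction and Discussion), and either the intensity or the seriousness of such events will not be held in the severity field. The other is the support for the two rules that turn on the word, because the article describes no other recorded field that classifies an event as serious.

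**Working it through.** The plan gives no figure to reproduce, and no rate, power or error level enters. The check sets the sentences side by side and counts what the list can hold.

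**Inputs**

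- Grading list, section 2.6: four levels under one label, severity.
- AE form, section 2.6: six kinds of entry, namely start date, end date, severity, relation to the trial, outcomes and action taken. None is a seriousness item.
- Participant-level rule, section 2.2: uses *serious*.
- Trial-level rule, section 2.6: uses *serious*, joined with relatedness and unexpectedness.

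**Step 1: what has to be recorded.** Three intensity levels and two seriousness states give 3 × 2 = 6 kinds of event.

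**Step 2: what the list offers.** It has 4 codes, so 6 kinds of event cannot each have their own code. The table shows where each kind goes under the two ways in which a rater could use the list.

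| Event | If *serious* is used for any event meeting an outcome criterion | If the rater codes by intensity |
|---|---|---|
| Mild, not serious | mild | mild |
| Moderate, not serious | moderate | moderate |
| Severe, not serious | severe | severe |
| Mild, serious | serious (intensity lost) | mild (not flagged) |
| Moderate, serious | serious (intensity lost) | moderate (not flagged) |
| Severe, serious | serious (intensity lost) | severe (not flagged) |

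**Step 3: what follows.** The three non-serious kinds are coded correctly under both uses. All three serious kinds lose something under either use. In the first column, the code identifies serious events but three intensities collapse into one code. In the second column, the intensity is kept but the code no longer separates serious from non-serious events. The article does not say which use is meant, and two raters could differ.

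**Step 4: link to the rules.** Under the first use, both rules could be served from the severity code. Under the second, the code would not bring a serious event to notice, and someone would have to recognise it from other information.

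**The case against.** The strongest reply is that this is a condensed article written in loose English. The AE form itself is not shown, and the full protocol may define serious events and provide a tick box for them. The absence of such a definition from a journal article would be no finding. The two rules also do not cite the grading list. The trial stop combines relatedness, unexpectedness and seriousness, as a standard safety-reporting category does, so investigators could apply both rules by the usual meaning of the word whatever the severity field shows. The outcome and action-taken entries could also reveal a death or an admission.

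Much of this stands. It limits the consequence: a serious event goes unflagged only if the rater codes by intensity, and even then other entries may bring it to light. It does not remove the fault, which lies in what the section states and not in what it omits. The sentence names the attribute as severity and lists seriousness as one of its levels, and only severity is carried onto the form as described. If the full protocol defines serious events by outcome, the two texts conflict and need reconciling.

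Three stronger readings are tempting, and the article does not support them.

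- A reader might infer that severe but non-serious events will be coded as serious and could wrongly trigger a safety action. The list has its own level for severe, and nothing in section 2.6 moves such events out of it.
- A reader might infer that tables comparing the groups on serious and severe events will be wrong. Section 2.5 names no adverse event outcome, and section 2.8 specifies tests only for primary and secondary outcomes. No such table is described.
- A reader might infer that, with 50 patients per group, one or two miscoded events would change a comparison of serious events. No such comparison is specified, and the article gives no event rates from which to calculate this.

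**Conclusion.** The point holds in a limited form. Section 2.6 puts an outcome-based attribute on an intensity scale, and no separate seriousness item appears among the form entries it lists. An event that is serious by outcome therefore either loses its intensity grade or is not flagged as serious by its code, while two rules in the article use the word.

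The size cannot be quantified from the article: it depends on how many serious events occur and on how raters use the list. Nothing here touches the primary outcome, the sample size or any analysis in section 2.8. It is a modest defect in data capture and terminology.

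The conclusion rests on three assumptions: each event receives one value from the list; the form is as section 2.6 describes it; and *serious* in the two rules carries its usual outcome-based meaning, at least for the trial stop. If the form already holds a separate seriousness field, only the wording of the article is at fault.

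**What to change.** Replace the single item with two fields: severity (mild, moderate or severe) and seriousness (yes or no, by criteria stated in the protocol). Amend the grading sentence in section 2.6 and its list of form entries to match.

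Reconcile the first suspension criterion in section 2.2 with the trial stop in section 2.6, so that *serious* has one stated meaning in both places. This asks only for a consistent term. The content of the suspension and stopping rules remains for the sponsor to decide.

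The cost is one extra field on the AE form and a short wording change in section 2.6, with a matching clarification in section 2.2. If the form already has the field, only the wording needs changing.
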